## Abstract

**Background:**

Despite the widespread use of inhalation therapy, patients with chronic obstructive pulmonary disease (COPD) frequently experience suboptimal disease control due to medication nonadherence, improper inhaler use technique, and inappropriate device selection, which collectively impair health-related quality of life (HRQoL). Pharmacist-led interventions may help address these gaps. Interventions based on the information-motivation-behavioral skills model and supported by digital tools can improve adherence and self-management. This study evaluates the efficacy of a multifaceted pharmaceutical care intervention for COPD delivered through digital tool support.

**Objective:**

The primary objective is to compare the change in HRQoL, measured using the St George’s Respiratory Questionnaire, between the intervention and control groups from baseline to 12 months. Secondary objectives are to assess changes in medication adherence (Test of Adherence to Inhalers), quality of life (EQ-5D-5L), COPD-related medical costs, and patient-reported pharmacy service experience.

**Methods:**

This 1-year cluster randomized controlled trial evaluates a multifaceted pharmaceutical care intervention in adults with moderate to very severe COPD (Global Initiative for Chronic Obstructive Lung Disease, stages 2-4) who have confirmed suboptimal inhaler practice but remain matched to an appropriate inhaler device based on peak inspiratory flow rate measured using a digital tool. In total, 34 hospital-based cough and wheeze pharmaceutical care clinics were recruited and randomized (1:1) to either an intervention or a control group. The target sample size is 15 patients per site. Participants in the intervention group will receive tailored support using electronic adherence monitoring, inhaler use technique assessments, and peak inspiratory flow rate to optimize device selection and self-management. Participants in the control group will receive usual pharmaceutical care. Descriptive statistics will be used to summarize participant characteristics and outcomes. Linear mixed effects models will be used to compare primary and secondary outcomes. Subgroup analyses will explore effects by age, sex, education level, place of residence, and smoking status. Pharmacy service survey data will be analyzed qualitatively.

**Results:**

The trial was registered on July 15, 2024. Recruitment started on November 9, 2024, and enrollment was completed by December 31, 2025. As of December 31, 2025, we enrolled 454 participants, of whom 16 (3.5%) had completed the 12-month follow-up. The trial is expected to be completed by December 31, 2026, with results planned for publication in 2027.

**Conclusions:**

This multifaceted, pharmacist-led pharmaceutical care intervention may provide a scalable model for improving COPD management and HRQoL. If effective, the digitally supported program, grounded in the information-motivation-behavioral skills model, could be implemented in more than 1000 cough and wheeze pharmaceutical care clinics nationwide.

**Trial Registration:**

Chinese Clinical Trial Registry ChiCTR2400086943; https://tinyurl.com/75a9phbw

**International Registered Report Identifier (IRRID):**

DERR1-10.2196/82806

## Introduction

### Background and Rationale

Chronic obstructive pulmonary disease (COPD) poses a substantial global public health burden because of its high prevalence and economic impact [1]. In China, approximately 100 million individuals are affected [2], and the country faces the largest projected COPD-related economic burden globally from 2020 to 2050 [3]. Without effective interventions, new COPD cases and deaths in China may increase 1.5-fold over the next 25 years [4].

Inhalation therapy, the cornerstone of COPD management, relies critically on correct device technique and sustained medication adherence to achieve optimal disease control [5,6]. However, suboptimal practices persist: inhaler use technique errors occur in 50% to 100% of patients [7-10], nonadherence rates range from 50% to 80% [7-10], and inappropriate device selection affects more than 80% of patients [11]. These factors collectively undermine treatment efficacy, leading to poor disease control and impaired health-related quality of life (HRQoL) [12-14]. Therefore, it is essential to ensure the appropriate choice of inhalation devices, provide training on inhaler use, and promote medication adherence in COPD management.

Pharmacist-led interventions offer promise in addressing these gaps. Meta-analyses confirm their effectiveness in improving inhalation techniques (risk ratio=1.85, 95% CI 1.57-2.17; *P*<.0001) and medication adherence (risk ratio=1.41, 95% CI 1.24-1.61; *P*<.0001) [15-19]. In addition, this approach has been found to be cost-effective, with a mean cost saving of £671.59 (US $906.65) per patient (95% CI −£1584.73 [−US $2139.39] to −£68.14 [−US $91.99]; *P*<.0001; GBP £1 [US $1.35]) [20]. Notably, interventions grounded in the information-motivation-behavioral skills (IMB) model that facilitates health behaviors show enhanced adherence outcomes [21,22]. Consequently, IMB model−based interventions may be worthy of clinical promotion and application [15]. Concurrently, digital tools (eg, real-time adherence monitoring and telehealth) have demonstrated efficacy in promoting self-management and HRQoL among patients with COPD [23-26].

Although previous studies have explored the clinical effectiveness and cost-effectiveness of medication management for COPD, several aspects need to be addressed in the future studies. First, there is limited research that explored the impact of medication management on HRQoL among patients with COPD in the hospital-based pharmaceutical clinic setting; existing studies have focused primarily on behavioral outcomes [15-20]. If such pharmacist-led interventions are to be implemented in clinical settings, it is crucial to comprehensively understand their impact on patients’ health. Second, insufficient attention has been paid to device-patient mismatch despite its high prevalence [27,28]. Third, integrated interventions that combine the IMB theory with digital tools for real-world implementation remain scarce. To improve disease management and deliver patient-centered care that enhances patients’ well-being, it is essential to leverage these advancements in medication management and to tailor approaches to address the most prevalent medication use issues.

### Objective

This cluster randomized controlled trial evaluates a digitally enhanced, multifaceted pharmaceutical care intervention delivered across 34 cough and wheeze pharmaceutical care (CWPC) clinics. This will be a parallel-group superiority trial with 1:1 allocation to the intervention and control arms. This study aims to assess the impact of intervention on HRQoL in patients with moderate to very severe COPD who have confirmed suboptimal inhaler practice but remain matched to an appropriate inhaler device. It addresses evidence gaps through theory-driven, digitally enhanced management of medication adherence, inhaler use technique, and device selection. The findings aim to support the broader implementation of multifaceted pharmaceutical care models for COPD across more than 1000 CWPC clinics in 29 provinces and municipalities in China.

## Methods

### Study Setting

The multicenter trial will be conducted in 34 certified CWPC clinics embedded in secondary or tertiary hospitals across mainland China. Participating sites are required to (1) hold CWPC accreditation with at least 2 licensed pharmacists trained in COPD management, (2) have access to all guideline-recommended inhalation therapies, and (3) have the capacity to implement protocolized interventions. A complete list of participating hospitals and their provinces and municipalities is provided in Table S1 in Multimedia Appendix 1. Thus, these accredited CWPC clinics, staffed by well-trained pharmacists, are well positioned to facilitate effective participant recruitment.

### Eligibility Criteria

Recruited participants must meet the eligibility criteria listed in Textbox 1.

Inclusion and exclusion criteria for participants.
**Inclusion criteria (all criteria must be met simultaneously)**
Aged 18 years or olderDiagnosed with chronic obstructive pulmonary disease, with severity of airflow obstruction from level 2 to level 4 (according to the Global Initiative for Chronic Obstructive Lung Disease grades) [6], defined as a forced expiratory volume in 1 second <80% of the predicted value after the use of bronchodilators (pulmonary function test results within 3 months could be used for screening)Suboptimal inhaler practice confirmed by at least 1 incorrect technique identified using a standard inhaler checklistAppropriate device-patient match (peak inspiratory flow rate–guided selection using digital sensors)Signed the informed consent form
**Exclusion criteria**
Inability to obtain informed consent from the patient or family membersComorbidities precluding participation, including terminal illness (life expectancy <6 months), active tuberculosis or lung cancer, or cognitive or physical impairment affecting inhaler usePregnancy or lactationConcurrent enrollment in other clinical trialsInability to complete the 12-month follow-up (eg, relocation plans)Other conditions in which the pharmacist who evaluated the participant is unable to comply with the trial

### Interventions

#### Intervention Arm

The intervention was systematically developed using the IMB model and comprises 7 core components mapped to this theoretical framework. The 7 components are introduction to therapeutic regimens, diversified information support, inhaler use technique training, medication adherence management, medication management using a diary booklet, follow‑up management, and interactive question-and-answer sessions (Table S2 in Multimedia Appendix 1). The digitally enhanced, multifaceted pharmaceutical care intervention is delivered during scheduled CWPC clinic visits at baseline and at months 1, 6, and 9 (Table 1). Each face-to-face intervention visit lasts approximately 30 minutes and follows a structured checklist (Table S2 in Multimedia Appendix 1).

**Table 1 table1:** Schedule of enrollment, interventions, and assessments (SPIRIT: Standard Protocol Items: Recommendations for Interventional Trials).

Time point		Baseline (−60 to 0 d; T0)	Month 1 (−14 to +14 d; T1)	Month 3 (−14 to +14 d; T2)	Month 6 (−14 to +14 d; T3)	Month 7 (−14 to +14 d; T4)	Month 9 (−14 to +14 d; T5)	Month 10 (−14 to +14 d; T6)	Month 12 (−14 to +14 d; T7)
**Enrollment**									
	Eligibility screen	✓							
	Informed consent	✓							
	Allocation (cluster level)	✓							
**Interventions**									
	Intervention arm	✓	✓		✓		✓		
	Control arm: standard CWPC^a^ pharmaceutical care	✓	✓		✓		✓		
**Assessments**									
	Visit date	✓	✓	✓	✓	✓	✓	✓	✓
	Telephone follow-up for questionnaire administration			✓		✓		✓	
	Basic information	✓							
	Medical history	✓							✓
	Physical examination	✓							
	Pulmonary function test	✓							✓
AECOPD^b^ status		✓	✓		✓		✓		✓
SGRQ^c^		✓	✓		✓		✓		✓
TAI-10^d^		✓	✓		✓		✓		✓
EQ‑5D‑5L^e^		✓							✓
COPD^f^ medication use in the past 2 wk		✓	✓		✓		✓		✓
COPD medication regimen at current visit		✓	✓		✓		✓		✓
Other concomitant medications in the past 2 wk		✓	✓		✓		✓		✓
Treatment costs of COPD		✓	✓		✓		✓		✓
Disease status			✓		✓		✓		✓
Pharmacy service survey									✓

^a^CWPC: cough and wheeze pharmaceutical care.

^b^AECOPD: acute exacerbations of chronic obstructive pulmonary disease.

^c^SGRQ: St George’s Respiratory Questionnaire.

^d^TAI-10: Test of Adherence to Inhalers.

^e^EQ‑5D‑5L: European Quality of Life-5 Dimensions-5 Level version.

^f^COPD: chronic obstructive pulmonary disease.

Clinical pharmacists at intervention sites will receive standardized training before study initiation (Figure 1), including instruction on the trial rationale and objectives, COPD pharmacotherapy and inhaler use, and detailed guidance on implementing each intervention component. Pharmacists in the intervention arm will also be trained to use the digital inhaler sensor and the peak inspiratory flow rate assessment system to support inhaler use technique training (Figure 2) and device selection (see method 1 in Multimedia Appendix 1).

**Figure 1 figure1:**
[figure not shown]
Overview of the study stages and implementation timeline. IMB: information-motivation-behavioral skills; SOP: standard operating procedure.

**Figure 2 figure2:**
[figure not shown]
Illustration of the selection of digital inhaler sensor devices for inhaler use technique training.

#### Control Arm: Standard CWPC Pharmaceutical Care

Sites allocated to the control arm will continue to provide standard CWPC pharmaceutical care according to existing practice. Pharmacists at participating sites will be trained on the standardized operating procedures (SOPs) corresponding to their allocation (Table S3 in Multimedia Appendix 1). At baseline and at months 1, 6, and 9, pharmacists will typically spend approximately 10 minutes per consultation (Table 1). Standard care includes (1) introduction to the therapeutic regimen (drug names, indications, and basic dosing instructions); (2) counseling on dosage and administration; (3) reminders regarding key drug precautions and management of common adverse drug reactions; and (4) demonstration and training in correct inhaler use technique using routine educational tools.

#### Strategies to Improve and Monitor Adherence to Intervention Protocols

To promote consistency of care within each study arm and to minimize contamination between arms, SOPs have been developed for both the intervention and control pharmaceutical care pathways (Tables S2 and S3 in Multimedia Appendix 1). Pharmacists at all participating sites will be trained in the SOPs corresponding to their allocation.

During the trial, completion of each digital-enabled pharmaceutical care component (intervention arm) or standard care element (control arm) will be documented in the electronic data capture (EDC) system using structured checklists (Tables S2 and S3 in Multimedia Appendix 1), which serve as fidelity-monitoring tools. The coordinating center will conduct periodic remote audits of EDC entries and, when necessary, on‑site or online supervision visits to provide feedback and reinforce protocol adherence. For patients, adherence to scheduled visits will be supported through automated appointment reminders delivered via the WeChat mini‑program.

#### Concomitant Care and Cointerventions

All COPD pharmacological treatments, including the choice and adjustment of inhalation therapies, will be prescribed at the discretion of the treating physicians in accordance with current Global Initiative for Chronic Obstructive Lung Disease (GOLD) guidelines and national guidelines. Other routine medical care for COPD and comorbid conditions (eg, vaccinations, pulmonary rehabilitation, and management of cardiovascular disease or diabetes) will be allowed and recorded as concomitant treatments.

### Study Outcomes

#### Primary Outcome

The St George’s Respiratory Questionnaire (SGRQ) will be used to assess HRQoL. The primary end point is the between-group difference in change from baseline to 12 months in the SGRQ total score, measured at baseline and 12 months after initiation of the intervention. The SGRQ was originally developed by Jones et al [29] and consists of 50 items divided into 3 sections: symptoms, activities, and impact. The scoring range is from 0 to 100, with a lower score indicating better health status in patients with COPD. SGRQ will be administered at baseline and at months 1, 6, 9, and 12 (Table 1).

#### Secondary Outcomes

##### Medication Adherence

The Test of Adherence to Inhalers (TAI-10) will be used to evaluate adherence to inhalation therapy. The main adherence outcome will be the between-group difference in change from baseline to 12 months in the TAI-10 score. The TAI-10 questionnaire was designed to assess the adherence to inhaler use in patients with asthma or COPD [30] and consists of 12 items. Items 1 to 10 assess the patient’s perspective and are scored on a 5-point scale (1=worst and 5=best). Items 11 and 12 reflect health care professional assessments and are scored on a 2-point scale (1=bad and 2=good). TAI assessments will be conducted according to the schedule shown in Table 1.

##### Generic Quality of Life

Generic health status will be assessed using the EQ-5D-5L, which covers 5 dimensions (mobility, self-care, usual activities, pain or discomfort, and anxiety or depression), each rated on 5 levels from *no problems* to *extreme problems* [31]. We calculated the EQ-5D-5L index using the value sets developed by Luo et al [32], with 1 representing the value of instrument-defined full health. The main EQ-5D-5L outcome will be the between-group difference in change from baseline to 12 months in the utility index. Measurement time points are shown in Table 1.

##### Pharmacy Service Survey

A pharmacy service survey will be used to assess patients’ perceived improvements in COPD-related and medication-related knowledge, self-reported quality of life, mastery of correct inhaler use after participation, and adequacy of communication with pharmacists (Table S4 in Multimedia Appendix 1). This survey will be administered at month 12 (Table 1).

##### Medical Cost

The medical cost will be collected using a microcosting approach [33] from the patient-level direct medical cost perspective over the 12-month trial period. At each scheduled visit, COPD-related direct medical expenses paid by patients will be recorded, including registration fees, examination costs, medication expenses, and other COPD-related medical service fees, when applicable. The primary economic outcome will be cumulative COPD-related direct medical costs per participant over 12 months, with the detailed data collection schedule provided in Table 1.

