#### Economic Evaluation

The EQ-5D-5L questionnaire will be used to obtain the health utility values for each participant before and after the intervention [32,34]. These values will be used to calculate the change in quality-adjusted life years (QALYs) over the 12-month follow-up for both groups [32,34]. The incremental cost-effectiveness ratio will be calculated as incremental cost divided by incremental QALYs. The willingness-to-pay per QALY threshold was set at 128,000 RMB (US $36,364) per QALY, equivalent to 1.76 times the gross domestic product per capita in China [35]. A 1-way sensitivity analysis will be conducted to assess the robustness of the model and the reliability of the results. All analyses will be performed using SAS (version 9.4; SAS Institute Inc).

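### The only cost defined for the ICER is what patients pay, so the added cost of delivering the intervention is left out while the ratio is read against a GDP-based threshold

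*Protocol article*

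**What the plan says.** All of this is in the protocol article.

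- **Perspective and method (Medical Cost).** Costs are taken "from the patient-level direct medical cost perspective over the 12-month trial period". The method is named: "The medical cost will be collected using a microcosting approach".
- **What is recorded (Medical Cost).** The rule is that "COPD-related direct medical expenses paid by patients will be recorded". This is done at every planned visit. The cost items are then listed, "including registration fees, examination costs, medication expenses, and other COPD-related medical service fees, when applicable".
- **Outcome (Medical Cost).** "The primary economic outcome will be cumulative COPD-related direct medical costs per participant over 12 months".
- **Ratio (Economic Evaluation).** "The incremental cost-effectiveness ratio will be calculated as incremental cost divided by incremental QALYs". The cost term is not defined again there. The threshold is 128,000 RMB per QALY, given as 1.76 times GDP per capita. A one-way sensitivity analysis is planned, and its parameters are not named.
- **Intensity of care.** In the intervention arm, "Each face-to-face intervention visit lasts approximately 30 minutes and follows a structured checklist". In the control arm, "pharmacists will typically spend approximately 10 minutes per consultation". Both schedules have visits at baseline and at months 1, 6 and 9.
- **Other inputs.** Intervention pharmacists receive additional training on the inhaler sensor and the inspiratory flow system (Intervention Arm). The sensors give voice prompts and record inhalations (Comparison With Previous Work).

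**The concern.** The two arms differ by design in what they cost to deliver, yet no delivery item appears among the recorded costs. The cost in Medical Cost is the only one defined, so it is the only candidate for the numerator of the ICER. Delivery inputs then count as zero unless a patient happens to be charged for them, and no section says that patients are.

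An ICER is compared with a threshold to judge whether the health gain is worth the resources spent. A threshold tied to GDP per capita speaks for a health system or society, and a patient-paid numerator does not measure what that decision-maker spends. The article looks ahead to use in more than 1000 clinics. Whoever funds those clinics would have to supply the pharmacist time, devices and training that the ratio leaves out.

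**Working it through.** The article states no incremental cost, QALY gain or ICER, so there is no figure of its own to reproduce.

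**1. Extra pharmacist time (document inputs only).**
- Visits: 4 (baseline, months 1, 6 and 9).
- Minutes per visit: about 30 in the intervention arm and about 10 in the control arm.
- Per participant: 4 x 30 = 120 against 4 x 10 = 40, a difference of 4 x (30 - 10) = 80 minutes.
- Over the planned intervention arm: 17 clinics x 15 = 255 participants, and 255 x 80 / 60 = 340 hours.

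**2. Direction.** Let C be the omitted incremental delivery cost per participant (C > 0) and dQ the incremental QALYs. Omitting C raises net monetary benefit, 128,000 x dQ - incremental cost, by exactly C whatever the sign of dQ. When dQ > 0, it lowers the ICER by C / dQ. This part of the bias therefore has one direction.

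**3. Possible size (assumed inputs).** None of these inputs is in the article: pharmacist cost 50 to 200 RMB per hour; sensors, platform and training 0 to 2,000 RMB per participant; dQ 0.01 to 0.05.

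| Case | C (RMB) | dQ | C / dQ (RMB per QALY) | Share of 128,000 |
|---|---|---|---|---|
| 50 RMB/h, other 0 | 80/60 x 50 = 67 | 0.05 | 1,333 | 1% |
| 200 RMB/h, other 0 | 80/60 x 200 = 267 | 0.01 | 26,667 | 21% |
| 100 RMB/h, other 1,000 | 133 + 1,000 = 1,133 | 0.02 | 56,667 | 44% |
| 200 RMB/h, other 2,000 | 267 + 2,000 = 2,267 | 0.01 | 226,667 | 177% |

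Pharmacist time alone gives 1% to 21% of the threshold across these ranges. Anything larger comes from the assumed sensor, platform and training cost.

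**4. Insurer-paid care (assumed inputs).** Suppose recorded expenses are out-of-pocket only. Take C = 1,000 RMB and dQ = 0.02, and let I be the between-arm difference in insurer-paid cost (intervention minus control). Counting both omitted parts shifts the ICER by (C + I) / dQ:
- I = +1,000: 2,000 / 0.02 = +100,000 RMB per QALY.
- I = -1,000: 0 / 0.02 = 0.
- I = -3,000: -2,000 / 0.02 = -100,000 RMB per QALY.

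The sign depends on I, about which the article says nothing.

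**The case against.** **The numerator is inferred.** Economic Evaluation does not say that the ICER uses patient-paid expense alone. Sensor purchase, training and wages would come from trial accounts, not from participants at visits, and a separate analysis or health-economic plan could cover them. This is fair as far as it goes, and it is why the point is conditional on the text being followed as written. But the article does more than stay silent: it states a perspective, a payer and a list of items, and delivery falls outside all three unless patients are charged for it.

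**The perspective is declared.** A patient perspective is legitimate in itself. What does not fit is reading its ratio against a GDP-based threshold.

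**Not every input is incremental.** This stands. Flow-guided device matching is an inclusion criterion for all participants. The WeChat appointment reminders are not described as specific to one arm. Pharmacists at all sites are trained on their own procedures. Only what differs between arms belongs in C.

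**A stronger reading is tempting.** A reader might infer that insurer-paid care is also valued at zero and that the whole ICER is therefore biased towards the intervention. The documents do not support this. Expenses paid by patients may mean the gross bill or the out-of-pocket share, and hospital medical records are also a data source. Even on the out-of-pocket reading the direction is open: averted exacerbations would make the omission count against the intervention, and greater medicine use would make it count in favour.

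**Roll-out is not tied to the ICER.** The article conditions adoption on effectiveness and disease burden, not on meeting the threshold. That is correct, and it limits the consequence to the economic conclusion.

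**Conclusion.** The point holds for delivery cost. As written, the ICER leaves out 80 extra pharmacist minutes per participant, the digital sensors and the additional arm-specific training, except for anything billed to patients. That omission can only make the intervention look better, and the resulting ratio should not be compared with 128,000 RMB per QALY.

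Only the 80 minutes comes from the document. Every RMB and QALY figure is assumed, and the resulting range, 1% to 177% of the threshold, runs from negligible to decisive, so it establishes no particular size. The net bias, once any unrecorded insurer-paid care is considered, cannot be signed. The SGRQ primary outcome is unaffected.

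**What to change.** 1. Define the base-case ICER cost from a health-system perspective as COPD-related medical charges plus incremental delivery cost.
2. Build delivery cost from three parts: pharmacist minutes by arm (visits documented in the EDC checklists x planned duration x wage), arm-specific sensor and platform cost, and arm-specific training cost spread over participants. Count only inputs that differ between arms.
3. State whether recorded expenses are gross charges or out-of-pocket payments. Use gross charges where bills or hospital records show them.
4. Keep the patient-paid version as a secondary perspective, and do not compare it with the threshold.
5. Report how the ICER changes over a stated range of delivery cost, for example within the planned one-way sensitivity analysis.

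Cost: a change of wording, a little extra costing work from the trial's own purchase and training records and existing checklists, and probably a less favourable ICER. Full retrieval of insurer-paid amounts across 34 hospitals would be more work. It is not needed to correct the delivery-cost omission.
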